**Method:**

A randomized, double-blind, placebo-controlled clinical trial is designed to study the efficiency and possible mechanism of action of probiotics for chronic constipation, in which 200 eligible volunteers with chronic constipation will be randomly assigned to a probiotic group (oral *Lactobacillus plantarum* P9 probiotic powder, 100 billion colony-forming units (CFUs)/day) or a placebo group. Volunteers, treatment distributors, data collectors, and data analysts will be blinded. The primary outcome is the weekly mean frequency of complete spontaneous bowel movements (CSBMs), and secondary outcomes include weekly mean frequency of CSBMs ≥3, weekly mean frequency of spontaneous bowel movements (SBMs), weekly mean stool appearance score, weekly mean difficulty of passing stool score, weekly percentage of volunteers who use auxiliary measures to assist with defecation (WPUAMA), quality-of-life (QOL) score, emotional status score, gut microbiome, and faecal metabolome. Each outcome measure will be assessed at the time points of preadministration (day 0), administration (day 14 and/or 28), and postadministration (day 42) to identify inter- and intragroup differences. Adverse events will be recorded to evaluate the safety of *L. plantarum* P9. *Discussion*. The protocol will provide methodological guidance for other similar studies, avoiding methodological bias and ultimately facilitating the formulation of consensus on the use of probiotics as a constipation-relieving agent. In addition, the results are more comprehensive than those of existing studies and may objectively and scientifically reflect the effectiveness of *L. plantarum* P9 on constipation. If the expected study findings are obtained, *L. plantarum* P9, taken as a probiotic, may become a complementary choice for chronically constipated patients. This trial is registered with Chinese Clinical Trial Registry (ChiCTR) (no. ChiCTR2000038396) registered on November 22, 2020, https://www.chictr.org.cn/showproj.aspx?proj=54024.

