### 2.4. Volunteer Recruitment

The investigators will recruit volunteers from the public through in-person communication, posters, and WeChat promotions. Volunteers can scan a WeChat two-dimensional (QR) code to register for enrolment, submit their personal information, and answer questions related to inclusion and exclusion criteria. Volunteers will undergo a procedure that includes three rounds of screening. First, the investigators will collect and collate the volunteers' registration information and, according to the information provided by registrants, invite potentially eligible candidates to participate in a central consultation with clinical specialists for further screening and selection of eligible volunteers. Second, during the central consultation, trained study implementers will introduce the trial to volunteers in the form of a video and information sheets describing the main aspects of the trial and discuss the information provided in the video and information sheets. Then, volunteers will meet with the clinical specialist to confirm their registration information, especially regarding inclusion and exclusion criteria. Third, volunteers will sign an informed consent form in the presence of a member of the data management team (DMT). Then, volunteers will undergo a 14-day screening period when they will not be allowed to take any medicines or health products to improve their constipation symptoms. Each volunteer will be asked to collect one stool sample and complete an online diary entry daily (Figure 2). At the end of the screening period, the diary and stool sample results will be reviewed and used to select eligible volunteers. Subsequent steps will include the formal intervention and follow-up visits (Figure 1).

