### 2.12. Sample Size

This study is a clinical trial during which volunteers will consume a sample medication or placebo for 28 days and will be followed up for 42 days. The primary outcome measure is the weekly frequency of CSBMs. The expected weekly frequencies of CSBMs on day 28 are 1.1 in the control group and 4.1 in the probiotic group, with a between-group difference of 3. Given a standard deviation *S* = 6, *α* = 0.05, and *β* = 0.20, the sample size should be at least 63 volunteers per group, as calculated with the formula for statistically significant effectiveness. After considering the drop-out rate (20% or lower), the sample size should be 76 or more participants per group. The final sample size will be 100 participants per group for a total of 200 volunteers.

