### 2.15. Statistical Analysis

The intention-to-treat (ITT) analysis will be conducted between the two groups. Then, the following four data sets will be used for the per-protocol (PP) analysis: (1) the data from all participants who completed the follow-up and (2) a subgroup analysis regarding levels of compliance (≥80%, 60–80%, and <60%) to validate the robustness of the results. The hypothesis will be tested using the methods described below during the ITT and PP analyses.

First, the Wilcoxon signed-rank sum test will be used for the outcome measures, including the weekly mean frequency of CSBMs, weekly mean stool appearance score, weekly mean difficulty of passing stool score, weekly mean frequency of SBMs, QOL score, and emotional status score, at each observation point to analyse the intergroup differences in each outcome measure. The chi-square (*χ*^2^) test will be used for the outcome measures, namely, the percentage of volunteers with a weekly mean frequency of CSBMs ≥3 and WPUAMA, at each observation point. In the analyses, the *P* value indicating statistical significance will be set to 0.05.

Then, the Kruskal–Wallis rank sum test will be used for multiple comparisons of outcome measures, including the weekly mean frequency of CSBMs, weekly mean stool appearance score, weekly mean difficulty of passing stool score, weekly mean frequency of SBMs, QOL score, and emotional status score, and the *χ*^2^ test will be used for multiple comparisons of outcome measures, including percentage of volunteers with a weekly mean frequency of CSBMs ≥3 and WPUAMA, at each observation point to identify the intragroup changing trends in consecutive phases, namely, pre-, during, and postprobiotic administration. In the analyses, the *P* value indicating statistical significance will be adjusted to 0.05/[*k* (*k* −1)/2], where *k* is the number of sample groups included in the comparison.

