We optimize the methodology from the following aspects: ① The general principle for a high-quality RCT is strictly obeyed through the participation of third-party independent companies or the DMT, including randomization, parallel control, blinding, allocation concealment, combination of ITT and PP analyses, consideration of withdrawals or dropouts, replication (enough observed study subjects), and other factors. ② The sample size (100 for each group) is obtained based on the expected difference in weekly frequency of CSBMs between the treatment group and control group, which is sufficient to ensure the reliability and accuracy of the results. The sample sizes in 33 of the 35 previous RCTs are dozens or even several participants, which is probably not sufficient to obtain an accurate result. ③ The latest Rome criteria (Rome IV for the present RCT) are suggested for the diagnosis of chronic constipation to avoid any other self-definition by researchers. ④ Multidimensional outcomes have been observed in the present RCT, including improvements in clinical symptoms, QOL score, emotional status score, and modifications in the gut microbiome and faecal metabolome, to produce a chain of evidence from causal improvements in metagenomic and metabolomic data to clinical symptoms and then to the emotional state and QOL. The outcomes are measured using accepted methods, e.g., BSFS [53], PAC-QOL [57], DASS-21 [58], next-generation sequencing, and LC–MS/MS analysis. Thus, the effects of probiotics on chronic constipation in the present study are more reliable and explainable. ⑤ Other key parameters, such as the study stage and duration, are also suggested.

In addition, the protocol is conducted to prove its feasibility and scientificity by studying the effects of *L. plantarum* P9 on chronic constipation. The study is articulated with a clear testable hypothesis stating that *L. plantarum* P9 improves the clinical symptoms and patient QOL by modifying the intestinal flora. Additionally, the safety of *L. plantarum* P9 will be assessed.

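### Section 2.15 lists within-arm before/during/after significance tests among the methods that test the hypothesis, although they contain no placebo contrast, and does not rank them below the between-arm tests or call them descriptive

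*Protocol article*

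**What the plan says.** In the protocol article, section 2.15 introduces its methods with one sentence: "The hypothesis will be tested using the methods described below during the ITT and PP analyses". Two families of tests follow.

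- The first compares the arms "at each observation point to analyse the intergroup differences in each outcome measure", at P < 0.05, with chi-square tests for the two percentage outcomes.
- The second applies Kruskal–Wallis and chi-square tests to the same clinical outcomes, the primary one included, "to identify the intragroup changing trends in consecutive phases, namely, pre-, during, and postprobiotic administration". The threshold is 0.05 divided by k(k−1)/2, "where *k* is the number of sample groups included in the comparison".

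The abstract gives the purpose of the repeated assessments as "to identify inter- and intragroup differences", without ranking the two. The hypothesis, stated in the Discussion, is causal: that "P9 improves the clinical symptoms and patient QOL by modifying the intestinal flora". Section 2.4 says of the screening period that "the diary and stool sample results will be reviewed and used to select eligible volunteers".

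**The concern.** A test of change over time inside one arm uses that arm's values only. It asks whether anything changed, not whether P9 changed more than placebo. Diary-reported bowel movements, quality-of-life and mood scores can all move in a placebo arm through expectation, natural fluctuation or selection at a bad moment. Every such change counts towards within-arm significance.

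The k(k−1)/2 divisor limits how many pairs of time points produce a false alarm when nothing changes. It does nothing about a real change that P9 did not cause.

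Section 2.15 presents these as tests of the hypothesis. A report that follows the article could therefore state that CSBMs or quality of life improved significantly during P9, or could contrast significance in one arm with non-significance in the other. Neither is a comparison of P9 with placebo.

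This is not a detail left to an unseen analysis plan. The article itself fixes the tests, their outcomes and their threshold.

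**Working it through.** **1. The plan's own figure.** Section 2.12 gives "The expected weekly frequencies of CSBMs on day 28 are 1.1 in the control group and 4.1 in the probiotic group", a difference of 3 with SD 6, alpha 0.05 and beta 0.20. Taking alpha as two-sided, n = 2(1.960 + 0.842)² × 6²/3² = 2 × 7.85 × 4 = 62.8, so 63 per group as stated. The trial is thus powered on a between-arm difference.

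**2. Within-arm threshold.** Four visits (days 0, 14, 28, 42) give 6 pairs and 0.05/6 = 0.0083 (critical z = 2.64). Three phases would give 0.05/3 = 0.0167 and higher rates than those below.

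**3. Inputs the article does not give.** Baseline mean, placebo change and within-person correlation ρ are all assumptions here. One bound exists: the placebo arm is expected at 1.1 CSBMs/week on day 28 and a count cannot start below 0, so the planned scenario allows a shared rise of at most about 1.1/week. The SDs tried are 6 (protocol), 2 (assumed) and 1.2. The last is roughly what a gamma-Poisson count implies with mean 1.1, shape 1.5 and averaging over two weeks: √(1.1²/1.5 + 1.1/2) = √1.36 = 1.17.

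**4. Chance of within-arm significance when P9 does nothing.** Let both arms rise by δ, with n = 100 per arm. The two-sample Kruskal–Wallis test treats the two visits as independent, so approximately

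rate ≈ Φ{[(δ/σ) × √(n/2) × √(3/π) − 2.64] / √(1 − ρ)}, with √(n/2) = 7.07 and √(3/π) = 0.977.

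- σ = 6, δ = 1: the shift is 1.15, so Φ(−1.49) = 7% at ρ = 0, Φ(−2.10) = 2% at ρ = 0.5, and 0.3% at ρ = 0.7.
- σ = 2, δ = 1: the shift is 3.46, giving 79%, 88% and 93%.
- σ = 1.2, δ = 0.5: the shift is 2.88, giving 60%, 63% and 67%.

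Simulation with normal data, same n and threshold:

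| SD | Shared rise per week | Day 0 v day 28, Kruskal–Wallis, ρ = 0 to 0.7 | Between arms at day 28, P < 0.05 |
|---|---|---|---|
| 6 | 1.0 | about 0–7% | about 5% |
| 2 | 1.0 | about 78–91% | about 5% |
| 1.2 | 0.5 | about 57–67% | about 5% |

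The between-arm column uses the two-sample rank-sum test.

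**5. A paired test is no remedy.** It is more sensitive to the same shared change. At SD 2, a rise of 0.5 and ρ = 0.5, the signed-rank test is significant in 40% of null trials against 10% for Kruskal–Wallis.

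**6. Contrasting the two arms' P values.** If each arm has probability p of significance and the arms are independent, exactly one is significant with probability 2p(1 − p). At p = 0.6 that is 48% of trials in which P9 has no effect.

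**7. Regression to the mean alone.** Suppose selection on a screening value below 3/week, SD 2 and no true change. With population mean 1.5 and ρ of 0.5, 0.7 and 0.85, the expected rises are 0.39, 0.23 and 0.12/week, and the Kruskal–Wallis test is significant in 4.9%, 0.2% and 0%. With population mean 2.5 and ρ = 0.5 the rate reaches 45%. But λ = φ(0.25)/Φ(0.25) = 0.646, so the follow-up mean would be 2.5 − 0.5 × 2 × 0.646 = 1.85/week, well above the planned placebo value of 1.1.

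**The case against.** The strongest reply is that no decision rule rests on the within-arm tests. Section 2.15 opens with a between-group ITT analysis and lists the intergroup tests first, section 2.12 powers the trial on a between-group difference, and nothing says efficacy may be declared from a within-arm P value alone. That stands, and it limits the harm. It does not undo the sentence that makes both families tests of the hypothesis.

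A reader might also infer more than the documents support:

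- **That only the probiotic arm is tested.** The wording about probiotic administration suggests it, but intragroup could equally mean each arm. Testing both would show a matching placebo trend, yet would still invite comparing two P values.
- **That regression to the mean makes the tests fire.** No CSBM cut-off for entry is stated. Section 2.2 uses fewer than 3 SBMs per week as one of six symptoms, of which two are needed. Within the planned placebo level, its effect under the planned test is small.
- **That false significance is near certain.** Shared rises of 2 or 3 per week would produce it even at SD 6, but they exceed the ceiling of about 1.1.
- **That comparing arms visit by visit is an error.** In a randomised trial it is a valid test of treatment effect. Comparing the arms on change is a refinement.

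At the protocol's own SD the problem is numerically small. However, an SD of 6 around a non-negative mean of 1.1 would need extreme skew, so smaller values deserve attention.

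**Conclusion.** The point holds in limited form. The article makes uncontrolled within-arm tests part of how a causal hypothesis is tested, and the multiplicity adjustment does not address what is wrong with them. The primary between-arm comparison is unaffected and keeps its error rate near 5%. Only efficacy statements based on within-arm significance are at risk.

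How often such a statement would be false cannot be fixed from the document. It runs from negligible (SD 6) to most trials (SD 2 with a rise of 1, or SD 1.2 with a rise of 0.5). These figures assume zero P9 effect, the same change in both arms, 100 analysed per arm, normal data and the four-visit threshold. This should be changed, but it does not invalidate the trial's main test.

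**What to change.** In section 2.15, state that the hypothesis is tested only by between-arm comparisons. Report the intragroup trends for both arms side by side as estimates with confidence intervals, labelled descriptive and without efficacy wording. Where change across phases is of interest, compare the arms on change from day 0, for example with a baseline-adjusted comparison or a rank-sum test on each volunteer's change. Align the abstract's stated purpose with this.

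The change is wording and analysis only, on data already being collected, and it does not affect the sample size. The cost is the loss of within-arm P values.

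### The all-pairs Bonferroni level in section 2.15 is attached to the Kruskal–Wallis and chi-square tests themselves, with no pairwise test named and k left open between 3 and 4

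*Protocol article*

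**What the plan says.** Section 2.15 has two layers of clinical testing. Between arms, each outcome is compared at each observation point at an undivided 0.05. Within arms, the stated aim is to find "intragroup changing trends in consecutive phases, namely, pre-, during, and postprobiotic administration".

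For the six frequency and score outcomes the within-arm step reads "the Kruskal–Wallis rank sum test will be used for multiple comparisons of outcome measures". For the two percentage outcomes, the chi-square "test will be used for multiple comparisons of outcome measures, including percentage of volunteers with a weekly mean frequency of CSBMs ≥3 and WPUAMA". The paragraph then says that in these analyses the P value for "statistical significance will be adjusted to 0.05/[*k* (*k* −1)/2"], and that k "is the number of sample groups included in the comparison".

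No value of k is given. The aim names three phases. The abstract's Method paragraph places assessments "at the time points of preadministration (day 0), administration (day 14 and/or 28), and postadministration (day 42"), and Table 1 marks days 0, 14, 28 and 42 for every diary and questionnaire outcome. So k could be 3 or 4.

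**The concern.** The divisor k(k−1)/2 is the number of distinct pairs among k samples. It is the right divisor when all pairs are tested and the familywise error is to stay at 0.05. A Kruskal–Wallis test, or a chi-square test on a table of k columns, gives a single P value for the hypothesis that all k samples are alike. One P value needs no division for pairs.

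Section 2.15 does not separate the overall test from a pairwise follow-up. An analyst who follows the text as written would hold the overall test to the divided level and lose power for no gain in error control. An analyst who infers a pairwise step must still choose k. A within-arm P value of 0.012 would be significant with k = 3 and not with k = 4. The rule covers all eight clinical outcomes listed in the section, including the primary one, in each arm, in both the ITT and PP analyses.

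**Working it through.** **Inputs.** From section 2.15: the formula 0.05/[k(k−1)/2], the two tests it is attached to, and the three phases. From the Method paragraph and Table 1: four observation points. From section 2.12: 100 participants per arm, used in the simulation.

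**Step 1: the threshold.**

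| k | pairs k(k−1)/2 | threshold | sum over all pairs |
|---|---|---|---|
| 2 | 1 | 0.05 | 0.05 |
| 3 | 3 | 0.05/3 = 0.0167 | 0.05 |
| 4 | 6 | 0.05/6 = 0.0083 | 0.05 |

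The formula is exactly the all-pairs Bonferroni level.

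**Step 2: the level applied to an overall test.** Take an overall test with nominal size whose statistic is chi-square with k−1 df. Choose the noncentrality λ that gives 80% power at 0.05, then recompute power at the divided level.

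- k = 4, 3 df: the critical value at 0.05 is 7.81, so λ = 10.90. At 0.0083 the critical value is 11.74 and power is 57.0%.
- k = 3, 2 df: the critical value at 0.05 is 5.99, so λ = 9.63. At 0.0167 the critical value is 8.19 and power is 66.0%.

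A null simulation (3000 runs, n = 100 per visit, normal data, independent visits) agrees. The overall Kruskal–Wallis test rejects in 0.053 of runs at 0.05 for both k = 3 and k = 4. At the divided level it rejects in 0.012 (k = 3) and 0.009 (k = 4).

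**Step 3: the level applied to pairs, with k the total number of phases or visits.** In the same simulation, two-sample tests of all pairs at the divided level give a familywise error of 0.049 (k = 3) and 0.041 (k = 4). Signed-rank tests on pairs, with an assumed within-person correlation of 0.5, give 0.046 and 0.047. The formula does its job here.

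**Step 4: k reset to 2 for each pair.** The divisor becomes 1 and every pair is tested at 0.05. The simulated familywise error is then 0.13 over 3 pairs and 0.21 over 6 (independent visits), with Bonferroni bounds of 3 × 0.05 = 0.15 and 6 × 0.05 = 0.30.

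**The case against.** The strongest defence is that the ordinary reading is sound. The text speaks of multiple comparisons and uses a pair count as divisor. Both point to pairwise tests among k phases or visits, and on that reading the level is valid all-pairs Bonferroni (step 3). This stands. A reader might infer that the threshold is wrong however it is read, and the documents do not support that.

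A reader might also infer that the correction vanishes, because a comparison of two visits includes two sample groups. The definition of k permits this, but it is strained: the text says the level is adjusted and sets it against the undivided 0.05 of the preceding paragraph, and with a divisor of 1 nothing would be adjusted. The figures in step 4 therefore show what the definition should rule out, not what the plan intends.

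Two further objections stand. Testing all six pairs is a legitimate choice, not an error, and comparing only with day 0 would drop the during-versus-post comparison that the phrase about consecutive phases calls for. And the article is condensed, so an analysis plan that is not shown may fix k and name the follow-up test; nothing here shows that the choice would be made after seeing the data.

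What the defence does not remove is that the article itself assigns the divided level to the two named tests and states no level for an overall test. That is a rule set down in the wrong place, not a detail left for later.

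**Conclusion.** The point holds as a misattached and incompletely defined threshold. Applied literally to an overall test, the division is unnecessary and costs about 23 percentage points of power with k = 4 (80% to 57%) or 14 with k = 3 (80% to 66%). Confined to pairwise comparisons, with k the total number of phases or visits, the formula is correct.

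The power figures assume an overall test with nominal size and a trend that would have 80% power at 0.05. They are not the power of the Kruskal–Wallis test on repeated measurements of the same people. In the simulation, with an assumed within-person correlation of 0.5, that test rejected at 0.05 in only 0.001 to 0.003 of null runs. That is a separate problem, and changing to paired tests would not by itself settle which level applies to which test.

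Severity is low. Only within-arm trend claims are affected. The between-arm comparisons, including the primary outcome, have their own 0.05 level and are unchanged.

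**What to change.** Replace the last sentence of the within-arm paragraph in section 2.15 with three statements:

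1. For each outcome and arm, one overall test across the observation points is judged at 0.05, with no division.
2. If it is significant, named pairwise tests follow. The article states whether the samples are the 3 phases or the 4 visits and lists the pairs in advance, keeping during versus post (for example day 28 against day 42) alongside the comparisons with day 0.
3. The multiplicity adjustment applies to those pairs only, by Holm's procedure. Holm holds the same familywise error as Bonferroni and is never less powerful. With all six pairs of four visits its thresholds run 0.05/6 = 0.0083, 0.05/5 = 0.0100, 0.05/4 = 0.0125, 0.05/3 = 0.0167, 0.05/2 = 0.025 and 0.05. With three phases they run 0.0167, 0.025 and 0.05.

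The smallest acceptable change keeps the present formula but confines it to the named pairwise tests and gives k as a number.

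The cost is a few sentences of analysis wording. No data collection, sample size or between-arm analysis changes.
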